# Effects of taichi on grade 1 hypertension: A study protocol for a randomized controlled trial

**DOI:** 10.1186/s13063-019-4028-6

**Published:** 2020-02-13

**Keywords:** Hypertension, Taichi, Taichichuan, Taijiquan, Martial arts, Blood pressure

## Abstract

**Background:**

Medication is generally recommended to reduce the morbidity and mortality caused by cardiovascular disease in hypertensive patients. However, considering the difficulties and economic factors associated with long-term medication, interest in taichi as an exercise treatment method has increased recently in Korean medical practice. Numerous studies have suggested that taichi can be used to treat various diseases and that is can affect psychosomatic factors such as anxiety. This study aims to evaluate the effect of taichi in reducing blood pressure among grade 1 hypertensive patients.

**Methods/design:**

In this randomized, active-controlled, assessor-blinded, two parallel-armed trial, 80 grade 1 hypertension patients will be recruited and randomly assigned to the usual care group or to the taichi group (*n* = 40 in each group). Subjects who voluntarily sign a study agreement will be educated in managing their own blood pressure by restricting salt intake, losing weight, moderating alcohol consumption, performing exercise, and regulating dietary intake at their first visit. In addition to self-management, the taichi group will perform two 60-min taichi sessions per week for a total of 8 weeks. Blood pressure will be measured as the primary outcome. In addition, body composition, heart rate, and the perceived intensity and difficulty of the exercise will be measured as secondary outcomes.

**Discussion:**

This study is a randomized controlled trial of taichi, which is not widely practiced in Korea. It may provide valuable data on the effects of taichi on hypertension, which will inform non-pharmaceutical treatment options for this disorder.

**Trial registration:**

Clinical Research Information Service, KCT0003632. Registered on 18 March 2019.

## Background

According to the Korea National Health and Nutrition Examination Survey (2015), the prevalence of hypertension is 27.9% in Korea, and 36.8% of Korean adults belong to the pre-hypertension category [1]. The prevalence of age-related hypertension was 52.1% in males and 51.5% in females aged 60–69 years, and 61.7% in males and 71.3% in females aged 70 years or older [1]. The higher prevalence in older patients is because age-related reductions in blood vessel elasticity increase the systolic blood pressure (SBP) and decrease the diastolic blood pressure (DBP) [2]. If blood pressure is not controlled, blood vessel damage will occur and lead to the complications of hypertension [2]. If hypertension is not detected early and treated properly, it can lead to complications such as myocardial infarction, stroke, and kidney failure [3].

The goal of controlling hypertension is to reduce the morbidity and mortality caused by cardiovascular disease by maintaining normal blood pressure [4, 5]. Medication for hypertension is generally recommended for SBP greater than 140 mmHg in patients younger than 60 years of age or DBP greater than 90 mmHg regardless of age [6]. However, considering the side effects and economic factors associated with long-term medication, non-medication approaches, such as eating healthily, exercising, ceasing smoking, and moderating alcohol consumption, are widely used to treat and manage hypertension along with pharmacotherapy [7]. In particular, Parker et al. [8] reported that physical activity, including moderate-intensity exercises such as walking or home exercise, reduced the blood pressure in incident hypertension after 15 years of follow-up.

In recent years, there has been increasing interest in taichi as an exercise treatment method for various diseases [9–15]. According to a study conducted by Kim [16], taichi may lower sympathetic tone and increase parasympathetic tone, which may result in changes in the autonomic nervous system. In addition, a randomized controlled study conducted by Tsai et al. [17] suggested that a 12-week period of taichi exercise reduces blood pressure, as well as lipid levels, and improves patient anxiety.

In this study, we analyze the blood pressure, heart rate, and body composition of grade 1 hypertension patients who have been diagnosed during a medical examination in a hospital or had an SBP of 140–159 mmHg or DBP of 90–99 mmHg in a screening test. We will evaluate the effectiveness of taichi by comparing the control of hypertension in a group practicing usual care with that in an experimental group practicing usual care plus taichi. The effectiveness of taichi for hypertension will, thus, be assessed in this randomized, active-controlled, assessor-blinded, two parallel-armed trial.

## Methods/design

### Study design

The proposed study is a randomized, active-controlled, assessor-blinded, two parallel-armed trial. It will be conducted at Pusan National University Korean Medicine Hospital (PNUKH) in Yangsan, Korea. The study protocol was approved by the institutional review board (IRB) of PNUKH on 16 January 2019 (approval number 2018014) and was registered in the Clinical Research Information Service on 18 March 2019 (KCT0003632). Table 1 is the schedule of enrollment, intervention, and assessments. Table 2 lists all relevant items in the World Health Organization’s trial registration data set.

**Table 1 Tab1:** Schedule of enrollment, intervention, and assessments

Measure	Screening (week 0)	Active treatment								Follow-up (12 weeks after screening)^†^
		Week 1	Week 2	Week 3	Week 4 (visit 1)^†^	Week 5	Week 6	Week 7	Week 8 (visit 2)^†^	
Study agreement	X									
Check for participation in other clinical trials	X									
Sociodemographic characteristics^1^	X									
Taichi exercises		Two sessions per week								
Body composition test	X								X	X
Measurement of vital signs^2^	X				X				X	X
Intensity and difficulty of exercises									X	
Number of taichi sessions attended										X
Adverse events					X				X	X

† ±3 days

^1^Age, gender, occupation, past history, present illness, and medications

^2^Blood pressure (systolic and diastolic), heart rate, and body temperature

**Table 2 Tab2:** All relevant items in the World Health Organization’s trial registration data set

Data category	Information
Primary registry and trial identifying number	Clinical Research Information Service, KCT0003632
Date of registration in primary registry	18 March 2019
Secondary identifying numbers	Not applicable
Source(s) of monetary or material support	Traditional Korea Medicine R&D program of Korea Health Industry Development Institute
Primary sponsor	Woosuk University
Secondary sponsor(s)	Not applicable
Contact for public queries	[name], [name], [contact]
Contact for scientific queries	[name], Department of Rehabilitation Medicine of Korean Medicine, Spine and Joint Center, Pusan National University Korean Medicine Hospital, [name].
Public title	Effects of taichi on grade 1 hypertension: A study protocol for a randomized controlled trial
Scientific title	The Effects of Taichi on Grade 1 Hypertension: Randomized controlled trial
Countries of recruitment	Republic of Korea
Health condition(s) or problem(s) studied	Hypertension
Intervention(s)	Taichi
Key inclusion and exclusion criteria	Inclusion Criteria o Patients must have been diagnosed with grade 1 hypertension during a health checkup or at the hospital, have SBP of 140 to 159 mmHg, or have DBP of 90 to 99 mmHg. o Patients who understand the study procedures and are able to follow the advice given o Patients must sign the study agreement and voluntarily agree to participate in the study Exclusion Criteria o Patients who have participated in another trial within a month before this study. o Patients whose high blood pressure is deemed by a doctor as too difficult to treat with exercise because of conditions such as severe pain or joint deformation. o Patients who are unable to communicate properly, for example due to dementia or mild cognitive impairment. o Patients who are pregnant. o Patients who should not be included in this study based on the investigator’s judgment.
Study type	Type of Study: Interventional Method of allocation: Randomized Masking: Outcome assessor blinding Assignment: Two-parallel armed, active controlled
Date of first enrollment	17 April 2019
Target sample size	1. Number of patients that the trial plans to enroll in total: 80 2. Number of patients that the trial has enrolled: 19
Recruitment status	Recruiting
Primary outcome(s)	Blood pressure, which will be measured at baseline, prior to each hospital visit, and during the follow-up visit
Key secondary outcomes	Body composition, which will be measured at baseline, week 8, and at the follow-up visit Heart rate, which will be measured at baseline, prior to each visit, and during the follow-up visit Intensity and difficulty of the exercises, which will be assessed once, at the end of the exercise training.
Ethics Review	1. Status: Approved 2. Date of approval: 16 January 2019 3. Name and contact details of Ethics committee: Pusan National University Korean Medicine Hospital IRB (approval number 2018014), [name], [name]
Completion date	15 January 2020
Summary results	Not applicable: protocol
Individual patient data sharing statement	1. Plan to share individual patient data: Decided 2. Plan description: The datasets used or analyzed during the study can be requested from the corresponding author

### Participants

#### Inclusion criteria

To be included, patients must meet all the inclusion criteria:
◦ They must have been diagnosed with grade 1 hypertension during a health checkup or at the hospital, have SBP of 140 to 159 mmHg, or have DBP of 90 to 99 mmHg.◦ They must understand the study procedures and should be able to follow the advice given ◦ They must sign the study agreement and voluntarily agree to participate in the study

#### Exclusion criteria

People who meet any of the exclusion cannot participate in the trial, that is
◦ If they have participated in another trial within a month before this study.◦ If their high blood pressure is deemed by a doctor as too difficult to treat with exercise because of conditions such as severe pain or joint deformation.◦ If they are unable to communicate properly, for example due to dementia or mild cognitive impairment.◦ If they are pregnant.◦ If they should not be included in this study based on the investigator’s judgment.

#### Discontinuation and dropout criteria

Participants will be withdrawn from the study:
◦ If they are found to have a previously undiagnosed severe disease after enrollment and before the start of the clinical trial.◦ If they have another disease (except hypertension) that may influence the results of the trial.◦ If they miss two consecutive assessment visits.◦ If they ask to be withdrawn from the trial.◦ If they are lost to follow-up.

### Recruitment

Patients will be recruited using advertisements on the bulletin boards of Pusan National University Yangsan Hospital (PNUYH) and PNUKH, at local public health centers, and at other local government offices. Patients who are interested in participating will first be screened to determine their eligibility. Eligible patients will receive an explanation of the study and can voluntarily decide whether they wish to participate. If the patient consents to the study terms, a clinical research coordinator (CRC) will check whether they are suitable in accordance with the inclusion and exclusion criteria. Then, the patient will be assigned randomly to the taichi group or the usual care group. After allocation, the CRC will schedule their treatment procedure. The first participant was enrolled on 17 April 2019.

### Randomization

A statistician who is not involved in conducting or assessing the clinical trial will generate a randomization sequence using the statistical program SAS®, Version 9.4 (SAS institute. Inc., Cary, NC). Using the sequence, the statistician will prepare 80 sealed envelopes, 40 of which will contain an A and 40 a B based on blocked randomization. Once a participant has signed the informed consent form, the CRC will open the next envelope in the sequence and inform the practitioner of the participant’s assignment to the experimental group or the usual care group (Fig. 1).

**Fig. 1 Fig1:**
[figure not shown]
Flowchart outlining the study timeline, including enrollment, allocation, follow-up, and analysis

### Blinding

Since blinding of the intervention is impossible, the group allocation will not be concealed and the participants will not be blind. Instead, the outcome assessor and data analyst will be blind to the allocation and they will not participate in recruitment or the intervention. The outcome assessor will assess participants at the study visits. The data analyst will analyze the statistical data to prevent selective reporting of outcome variables. Unblinding will be permitted only when it is necessary to reveal the participant’s allocated intervention, such as in cases of severe side effects, at the discretion of the assessor.

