### Outcome assessment

At the initial screening visit, the CRC will explain the study protocol to the patient. Then, the participants will be asked about their sociodemographic characteristics, including age, gender, occupation, past history, present illness, and medications, at an isolated room for allocation concealment. All adverse events will be recorded, and the practitioners will check the severity of the events and decide the continuance of the trial. Follow-up assessments will be performed once at 12 weeks after the initial screening visit (Table 1, Fig. 1).

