### Safety

Because the intervention is a simple exercise rather than untested drugs or medical devices, we do not expect any adverse events will be caused by the general Korean medical treatment. However, the investigators will inform the participants of all possible adverse events that may occur after taichi and instruct them to report any such adverse events. All adverse events recorded during the research period will be analyzed and reported. In general, due to the interventional characteristics of exercise, simple muscular pain may occur. We will provide beverages such as bottled water or green tea during the exercise sessions for the participants. To prevent falls and severe muscle aches, a chair will be available during exercise sessions. There will also be a space where participants can sit and relax. If a direct injury occurs in connection with this study, appropriate medical action may be taken, as determined by the investigator.

A data monitoring committee (DMC) comprising members of staff from the clinical research service institution (Woosuk University) will periodically monitor the study by telephone, e-mail, and visits, if necessary. The DMC will be composed of one statistician and one specialist in clinical research methodology. They will review the progress of the study and check all case report forms. In addition, they will check whether the study has followed the study protocol. If a problem is identified, the DMC will modify the protocol if necessary. If modifications to the protocol are required during the study, the modified protocol will be submitted by the clinical trial review committee to the IRB for approval. However, neither auditing nor an interim analysis are planned during the trial.

Additionally, as we will not collect any biological samples and do not intend to use the participants’ data in future studies, we do not need any additional consent for collection and use of participant data or biological specimens in ancillary studies. In accordance with government regulations and standards, all documents related to the conduct of a clinical trial must be kept by the director of clinical research, or the director of the institution and the clinical research manager, for at least 3 years after the completion of the clinical trial.

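### Unblinding is left to the outcome assessor, who is meant to stay blind, and on the stated roles it has no evident safety function (minor)

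*Protocol article*

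**What the plan says.** All references are to the protocol article.

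- **Blinding**, on who is blind: "the outcome assessor and data analyst will be blind to the allocation and they will not participate in recruitment or the intervention". The section has the outcome assessor see participants at the study visits.
- **Blinding**, on participants: "the group allocation will not be concealed and the participants will not be blind".
- **Blinding**, on unblinding: "Unblinding will be permitted only when it is necessary to reveal the participant’s allocated intervention", and then "such as in cases of severe side effects, at the discretion of the assessor".
- **Randomization**: "the CRC will open the next envelope in the sequence and inform the practitioner of the participant’s assignment".
- **Outcome assessment**, on adverse events: "the practitioners will check the severity of the events and decide the continuance of the trial".
- **Safety**, on injury connected with the study: "appropriate medical action may be taken, as determined by the investigator".
- **Primary outcome measurements**: the CRC takes blood pressure with an automatic monitor, and the mean of three readings is the outcome. The primary endpoint is week 8.
- **Table 1**: adverse events and vital signs are both scheduled at weeks 4, 8 and 12.

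**The concern.** An emergency code break exists so that someone who must act on an event, and lacks the allocation, can learn it. In this trial the discretion sits with a person whose only stated task is to measure outcomes without knowing the arm. To decide whether the arm must be revealed, that person has to hear about the event. For an injury in an exercise session, the account alone may give the arm away.

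Participants cannot be blinded, and the Discussion names this as a major limitation. Assessor blinding is therefore the main declared protection against bias in measurement, and it is part of the trial's design label. Any loss would tend to be one-sided, because the harms that the Safety section anticipates (muscular pain, falls) arise from the taichi sessions. A patient unblinded before week 8 would have the primary reading taken without blinding, and the week 12 reading as well.

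**Working it through.** **1. Who knows the arm, and who has a safety task**

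| Role | Knows the arm? | Stated safety task |
|---|---|---|
| Participant | Yes (Blinding) | Reports events (Safety) |
| CRC | Yes, opens the envelope (Randomization) | None stated |
| Practitioner | Yes, told by the CRC (Randomization) | Judges severity and continuance (Outcome assessment) |
| Investigator | Not stated | Determines medical action (Safety) |
| Outcome assessor | No (Blinding) | None, apart from the discretion to unblind |
| Data analyst | No (Blinding) | None |

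The two roles stated to be blind are the outcome assessor and the data analyst, and neither has a safety task that needs the arm. The investigator's knowledge of the arm is not stated, but the participant and the practitioner can both supply it. No stated safety task therefore depends on the assessor learning the arm.

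**2. Number of patients affected**

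The article gives no figure for severe events or unblinding, so there is no stated result to reproduce on this point. The only figure used is the 40 patients per group. It is consistent with the Sample size section: an effect size of 0.67, power 0.80 and two-sided 5% give 35.96, so 36 per group (exact noncentral t), and 36 / (1 − 0.10) = 40.

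Assume that 1–5% of one arm have a severe event and are unblinded:

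- 0.01 × 40 = 0.4
- 0.05 × 40 = 2

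That is 0–2 patients.

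**3. Effect on the arm mean**

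Shift in arm mean = (patients unblinded / 40) × bias per reading. Assume a bias of 2–5 mmHg in each affected patient:

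- 1 patient: 1/40 × 2 = 0.05 to 1/40 × 5 = 0.125 mmHg
- 2 patients: 2/40 × 2 = 0.10 to 2/40 × 5 = 0.25 mmHg
- 4 patients, beyond the range in step 2: 4/40 × 2 = 0.20 to 4/40 × 5 = 0.50 mmHg

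Both the counts and the bias are assumptions. No sample size or other stated figure changes.

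**4. Who takes the primary outcome**

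Blinding says that a blinded outcome assessor, who takes no part in recruitment, assesses participants at the visits. Primary outcome measurements says that the CRC takes blood pressure. Under Recruitment and Randomization the CRC checks eligibility and opens the envelope. Both descriptions cannot hold for blood pressure. If the CRC takes the readings, they are unblinded for every participant, whether or not a severe event occurs.

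**The case against.** Several points on the other side stand.

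- **The rule is conditional.** Unblinding is allowed only when necessary. If nobody needs the arm, the condition is never met and the sentence does little. A reader might infer that every severe side effect unblinds the remaining blood pressure readings. The text does not say so, and a code break would reach only that participant's later visits.
- **The readings are automatic.** The mean of three readings from an automatic monitor leaves an assessor limited room to influence the result.
- **The roles do not plainly collide.** A reader might infer that the site cannot tell who acts on a severe event. The three sections cover different decisions: unblinding, severity and continuance, and medical action.
- **Informal unblinding is not shown.** A reader might assume that 20–40% of taichi patients report muscular pain and conclude that 8–16 of 40 reveal their arm at a visit. The documents support neither the rate nor the step from report to disclosure. Table 1 does not say who asks about events, practitioners check their severity, and both groups are advised to exercise, so an ache does not by itself identify taichi.
- **The visit order may be partly right already.** Blood pressure is described as measured prior to the week 4 and week 8 visits, which suggests that it precedes other procedures. Something heard at week 4 could still carry over to week 8.

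These points limit the size of the problem. None of them gives the blinded assessor a reason to hold the discretion.

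**Conclusion.** The point holds as a minor one. The plan gives the unblinding decision to a role that it requires to stay blind, while the staff who judge adverse events already know the arm. On the stated roles the provision has no evident safety function and can only cost blinding for the participant concerned.

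The likely size is 0–2 patients of 40 and an arm-mean shift of at most about 0.25 mmHg, on the assumed 1–5% rate and 2–5 mmHg bias. The verdict assumes that the assessor in the unblinding sentence is the outcome assessor of the same section.

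A reader might go further and say that this sentence removes blinding from the primary outcome. The documents do not support that. Under Primary outcome measurements the readings are taken by the CRC, who knows every participant's arm, so blinding of blood pressure is already in doubt for a separate and larger reason.

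**What to change.** 1. In Blinding, replace the unblinding sentence. State that the outcome assessor and the data analyst stay blind throughout, that adverse events remain with the staff named under Outcome assessment and Safety, and that anyone who needs the allocation gets it from staff who already hold it, not through the assessor.
2. At weeks 4, 8 and 12, take blood pressure before adverse events are asked about, and have someone other than the blinded assessor ask. Record any accidental unblinding of the assessor, with the date and visit.
3. Reconcile Randomization, Blinding and Primary outcome measurements so that the person who takes blood pressure is blind to allocation. Without this, the first two changes do not protect the primary outcome.

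The first two changes cost one sentence and a fixed order of procedures. The third may mean giving the readings to someone other than the CRC who opens the envelopes. The sample size and the analysis do not change, and no information is withheld from those who care for participants.
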